### 2.4. Interventional therapy and intraoperative evaluation

Angiography of 4 branches of the whole brain (bilateral common carotid arteries and bilateral vertebral arteries) will be performed to evaluate the primary compensation of the diseased vascular area (circle of Willis compensation: whether the posterior and/or anterior communicating arteries are open). The operation then begins with the use of an embolus protection device. After carotid artery occlusion is expanded by a percutaneous transluminal angioplasty balloon, the catheter will be guided through the internal carotid artery occlusion segment, and intracranial vascular thrombectomy and recanalization will be performed using classical thrombectomy techniques. After successful opening of the occluded vessel or thrombus retrieval, observation will be performed for 30 minutes, and common carotid angiography (lesion vessel assessment angiography) will be repeated to assess the extent, stability, and changes in stenosis at the beginning of the internal carotid artery, in parallel with DynaCT (to confirm the presence of intracranial hemorrhage or contrast spillage). Finally, the next procedural step (whether to place a carotid stent and/or apply antiplatelet agents) will be performed according to the treatment plan decision maker’s instructions.

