### 2.5. Treatment plan recommendation and determination

Three surgical options are currently available. Stent placement + immediate normal application of antiplatelet drugs; Stent placement + delayed application of antiplatelet drugs; and no stent placement. “Immediate normal antiplatelet medication” refers to an intravenous tirofiban loading dose before stent placement and continuous intravenous pumping (calculated by kilogram of body weight according to the instructions) until 24 to 48 hours after surgery, followed by aspirin (100 mg), clopidogrel (75 mg), and oral quaque die. Delayed application of antiplatelet drugs means that 24 to 48 hours after surgery, when the condition is stable, as indicated by CT review, aspirin (100 mg) + clopidogrel (75 mg), and oral quaque die will be administered.

The ECASES assessor, a nonsurgical participant, will evaluate each subject (study or control group) according to the ECASES scoring rules (see below) and make ECASES treatment recommendations to the protocol decision maker; the surgeon and their assistant will evaluate and discuss each subject (study or control group) based on their experience and make treatment recommendations to the protocol decision maker. The ECASES assessor and surgical participants will be unaware of their respective treatment recommendations, and the decision maker will select a treatment plan based on subject grouping (ECASES recommendations for the study group/operator’s experience for the control group) and inform the operators of the finalized treatment plan for the next operation; however, they will not inform the operator of the source of the regimen (derived from the ECASES system or operator’s experience) and the subject subgroup.

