Cerebral edema: According to postoperative CT results, edema is classified into 4 conditions: no edema, mild edema (focal edema up to one-third of the hemisphere), moderate edema (focal edema greater than one-third of the hemisphere), and severe edema (edema with midline shift).^[10]^ Signs of focal edema are defined as narrowing of the cerebrospinal fluid space, for example, effacement of the cortical sulci or ventricular compression.^[11]^Modified treatment in cerebral infarction (mTICI) grading: The mTICI grading will be assessed based on DSA of the responsible vessel at the end of the procedure to evaluate the effectiveness of surgical revascularization.New cerebral infarction: Postoperative MRI-DWI sequences showed a new cerebral infarction (compared with the preoperative).Reocclusion of the responsible vessel: A responsible artery with an immediate postoperative mTICI classification ≥ 2b and a CTA, MRI, and/or DSA examination within 90 days postoperatively, suggesting artery reocclusion, will be defined as reocclusion of the responsible vessel.

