## 3. Discussion

Acute carotid stenting procedures associated with arterial thrombectomy have been performed by many neurointerventionists. The TITAN study, a retrospective pooled analysis of data from acute ischemic stroke patients with tandem lesions in the anterior circulation from 18 international comprehensive stroke centers (including more than 450 patients), showed that acute stenting of an extracranial internal carotid artery lesion was associated with improved reperfusion (mTICI 2b-3 and mTICI 3)^[12,13]^ without an excess risk of intracranial hemorrhage or mortality,^[14]^ as previously reported in 2 meta-analyses of case series.^[15,16]^ However, prospective controlled data are lacking regarding the efficacy and safety of carotid stenting in the acute phase of stroke reperfusion, particularly in the context of antiplatelet therapy.

According to research studies and work experience, intracranial hemorrhage is related to the preoperative infarct size, infarct site (basal ganglia area), contrast medium extravasation, or bleeding detected by intraoperative DynaCT after vascular recanalization in acute stroke with large-vessel occlusion.^[17,18]^ Postoperative recovery of neurological function (improvement of cerebral ischemia) is related to postoperative vascular patency and collateral circulation compensation.^[19]^ Accordingly, the ECASES system proposes a bleeding risk score and an ischemic risk score based on the above factors and then suggests an individualized stenting decision by weighing bleeding and ischemic risks with a sufficient theoretical basis. This study uses a randomized, double-blind design in which, for each subject, 2 types of stenting options from the ECASES system and expert experience are provided by investigators, and the stenting option is selected by a dedicated person (nonsurgical participant) according to the subject group. This person then informs the surgical staff, but the source of the option is not revealed, which minimizes confounding factors and bias and results in a reasonable and reliable study design. Additionally, ECASES uses a scale format that can realize specific and quantitative evaluations, and is accurate, fast, and efficient.

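### End-of-procedure mTICI is a valid between-group outcome but an imprecise one: a grade read before the stent instruction would remove noise from the shared thrombectomy step

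*Protocol article*

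**What the plan says.** Section 2.8 lists mTICI among the secondary outcomes and fixes when it is read: "The mTICI grading will be assessed based on DSA of the responsible vessel at the end of the procedure". Its stated purpose is "to evaluate the effectiveness of surgical revascularization".

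Section 2.4 gives the order of the operation. After balloon dilation of the carotid occlusion, "intracranial vascular thrombectomy and recanalization will be performed using classical thrombectomy techniques". Then: "After successful opening of the occluded vessel or thrombus retrieval, observation will be performed for 30 minutes", with repeat common carotid angiography and DynaCT. Only after this do the arms separate: "the next procedural step (whether to place a carotid stent and/or apply antiplatelet agents) will be performed according to the treatment plan decision maker’s instructions". Section 2.5 explains how that instruction depends on the arm: "the decision maker will select a treatment plan based on subject grouping (ECASES recommendations for the study group/operator’s experience for the control group"). The operators are told neither the source of the plan nor the patient's group.

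Section 2.12 specifies a chi-squared test for count data and a t test or Mann–Whitney test for measurement data. None of these adjusts for anything. No mTICI grade before the instruction is described.

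**The concern.** Everything that restores intracranial flow by thrombectomy happens before the arms differ. A patient whose thrombectomy fails, or succeeds fully, brings that result into the final grade whichever plan is chosen afterwards. The final grade therefore mixes two things: the result of a step common to both arms, and any change produced by the randomized step.

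Precision is at stake. If the plan chosen under ECASES raises or lowers reperfusion, that shift has to be seen against the patient-to-patient spread in thrombectomy success. A grade read just before the instruction would account for much of the spread. It is also a sound covariate: care up to that point is the same and the operators do not know the group, so the arm cannot influence it. If it is not recorded prospectively, a later analysis plan can adjust for it only by re-reading stored images.

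**Working it through.** The plan states no figure for mTICI, so there is none to reproduce. The calculation below is an illustration for mTICI dichotomized at 2b or better.

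**Inputs**
- Patients per group, n = 96. This is 101 per group (section 2.11) less the plan's 5% loss: 101 × 0.95 = 95.95.
- Proportion at mTICI 2b or better, p = 0.80, before and after the instruction. *Assumption.*
- Fraction changing status between the pre-decision run and the end of the procedure, c = 2%, 5% or 10%, half upward and half downward, so no net effect. *Assumption.*

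**Step 1: unadjusted comparison.** SE = √[2p(1 − p)/n] = √(2 × 0.8 × 0.2/96) = 0.0577, or 5.8 points. The 95% half-width is 1.96 × 5.77 = 11.3 points.

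**Step 2: correlation between the two grades.** The share at 2b or better on both occasions is p − c/2. The covariance is (p − c/2) − p² and the correlation is ρ = covariance/[p(1 − p)] = [(0.80 − c/2) − 0.64]/0.16.

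**Step 3: adjusted comparison.** With linear adjustment, SE(adjusted) = SE × √(1 − ρ²), and the variance falls by the fraction ρ².

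| c | ρ | ρ² (variance removed) | Adjusted SE (points) | 95% half-width (points) |
|---|---|---|---|---|
| 2% | 0.15/0.16 = 0.937 | 88% | 2.0 | 3.9 |
| 5% | 0.135/0.16 = 0.844 | 71% | 3.1 | 6.1 |
| 10% | 0.11/0.16 = 0.687 | 47% | 4.2 | 8.2 |

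**Step 4: sensitivity to n.** mTICI is read in the procedure room, so 90-day losses should not reduce it. With n = 101 the unadjusted SE is √(0.32/101) = 5.6 points (half-width 11.0). The adjusted values scale by √(96/101) = 0.975, to about 2.0–4.1 points. The conclusion is unchanged.

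**Step 5: is the unadjusted test valid?** A simulation of the chi-squared test with 101 per arm, 70% or 80% at 2b or better and no effect of the instruction rejected in 4.9–5.2% of trials. The nominal 5% holds.

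**Step 6: how insensitive is the unadjusted test?** This depends on how often the two recommendations differ in a way that changes stenting, and on how far stenting moves the grade. The document gives neither. Taking a net stenting contrast in 20–60% of patients and a shift of 10–20 points among them (assumptions), the net arm difference is 0.2 × 10 = 2 to 0.6 × 20 = 12 points. Simulated power is then about 6% to 71%.

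**The case against.** **The outcome is legitimate as it stands.** The final angiogram follows the randomized step, and the article gives a reason to expect that step to matter. The discussion cites pooled retrospective data in which "acute stenting of an extracranial internal carotid artery lesion was associated with improved reperfusion (mTICI 2b-3 and mTICI 3"). Treatment shared before the arms diverge adds variance and no bias. This stands in full.

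**A stronger reading is tempting.** A reader might infer that the comparison mostly reflects chance differences in thrombectomy success, or that such an imbalance would be passed off as an ECASES effect. The documents do not support this. Randomization makes the imbalance random error, which the test already allows for (step 5). Whether chance dominates cannot be settled without the discordance rate and the stent effect (step 6).

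**The size rests on assumptions and is partly self-limiting.** A small change fraction gives the largest variance reduction but also caps the effect available to find. If 2% change, all in one direction and in one arm only, the difference is about 2 points against an adjusted half-width of 3.9. At 10% it is about 10 points against 8.2. This also stands: adjustment improves precision but does not guarantee that an effect can be detected.

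**The 30-minute run may not be gradable.** Section 2.4 describes it as common carotid angiography to assess the stenosis at the origin of the internal carotid. It does not say that the intracranial territory is shown. This stands, and the fix allows for it.

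**It belongs in an analysis plan not shown.** This does not fully answer the point. The article itself fixes the time of the reading and names unadjusted tests, and the missing element is a measurement made during the procedure, not a detail of analysis.

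**Conclusion.** The point holds as one of precision only. The end-of-procedure comparison is valid, keeps its type I error rate and serves its stated technical purpose. It is less precise than it could be, because thrombectomy success is settled before the arms diverge and is left in the error term.

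With 80% at mTICI 2b or better, 96 per group and 2–10% changing status without net effect, adjustment lowers the standard error from 5.8 to about 2.0–4.2 points, a variance reduction of 47–88%. The 80% and the 2–10% are assumptions that the document neither gives nor contradicts. The gain shrinks as more patients change grade after the instruction. This is a cheap improvement to one secondary outcome and does not touch the primary outcome.

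**What to change.** In sections 2.4 and 2.8, keep the end-of-procedure grade, which is also the entry condition for the reocclusion outcome. Add a second mTICI grade, by the same reader and without knowledge of the group, on the last intracranial run before the decision maker's instruction. Use the 30-minute run for this only if it shows the intracranial territory.

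In section 2.12, compare the final grade between groups adjusted for the pre-decision grade, and tabulate by group the patients whose grade rose or fell after the instruction. An ordinal or logistic model would serve. If very few patients change status (at 2%, 96 × 0.02 is about 2 per group), a logistic fit may be unstable, and an adjusted risk difference is safer.

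The cost is one extra grade per patient, one case report form field and one model term. The drawback is reliance on a post-thrombectomy intracranial run that the article does not explicitly describe, so the protocol should say which run is to be graded.

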### 2.9. Data management system

All cases included in the study will be entered into the case report form by responsible evaluators within 48 hours and entered into the spreadsheet within 1 week. To clarify the person responsible, all persons entering the case report form will sign this form. A data supervisor who is not involved in the clinical study will check the data; when incorrect data are found, the original data will be searched and corrected in a timely manner. The date and person making the changes should be recorded to ensure that the data are error free.

### 2.10. Data security and monitoring board

To ensure the integrity of the clinical trial and protect the rights and health of the subjects, a data and safety monitoring committee is established for this study. Monitoring visits to clinical sites will be conducted periodically during the study to ensure that all aspects of the currently approved protocol/amendments are followed.

### 2.11. Sample size estimation

Assuming a rate of good neurological function in both the study and control groups (180 d) of not less than 51%, a noninferiority threshold Δ=–10%, a sample ratio of the study and control groups of 1:1, a unilateral test level (α = 0.025), a total certainty of 80%, and a 5% loss rate, the total sample size required is 202 patients and 101 patients in each group.

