### 2.7. Postoperative evaluation and patient follow-up

1)Imaging evaluation and follow-up.•CT: 3 planned CT examinations will be performed on the first, third, and 7th to 14th day after surgery. Additionally, CT examinations will be performed at any time according to the disease condition to evaluate intracranial hemorrhage and cerebral edema.•MRI: A planned MRI examination will be performed on the 3rd to 7th days after surgery, and examinations will be performed at any time according to the disease condition to evaluate new cerebral infarction and other conditions.•Vascular imaging examination: 2 planned CTA, MRA, and/or DSA examinations will be performed on the 90th day, 7 to 14 days after the operation, and at any time according to the disease condition to evaluate the reocclusion of the responsible vessels.2)Neurological function assessment and follow-up.

Patients will undergo follow-up evaluation on days 1, 7, 30, and 90 after surgery, and the NIHSS and mRS scores will be assessed.

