### 2.8. Study outcomes

Primary outcome: Neurological functional status at 90 days postoperatively

Patient neurological functional status will be assessed by mRS and NIHSS scores.

Secondary outcomes.

Changes in neurological function are classified as improved (postoperative NIHSS score decrease ≥ 4 points compared with preoperative), worsened (postoperative NIHSS score increase ≥ 4 points compared with preoperative), or stable (postoperative NIHSS score change < 4 points).Hemorrhage events: For the classification of bleeding events, we refer to ECASS II.^[9]^ Hemorrhagic events were classified according to the clinical and CT criteria. Hemorrhagic infarction 1 (HI1) was defined as small petechiae along the margins of the infarct, and hemorrhagic infarction 2 (HI2) as confluent petechiae within the infarcted area but no space-occupying effect.

parenchymal hemorrhage (PH1) as blood clots in 30% or less of the infarcted area with some slight space-occupying effect, and parenchymal hemorrhage (PH2) as blood clots in more than 30% of the infarcted area with a substantial space-occupying effect. Symptomatic intracranial hemorrhage was defined as blood at any site in the brain on the CT scan (as assessed by the CT reading panel, independent of the assessment by the investigator), documentation by the investigator of clinical deterioration, adverse events indicating clinical worsening (e.g., drowsiness, increase of hemiparesis), or a decrease in the NIHSS score of 4 or more points.

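### The sample size and margin are set on a 180-day good-function rate, but the primary outcome is mRS and NIHSS scores at 90 days and no later neurological assessment is planned

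*Protocol article*

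**What the plan says.** Four places in the protocol article bear on this point.

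- **Section 2.11 (sample size).** The calculation opens with "Assuming a rate of good neurological function in both the study and control groups (180 d"). The rate is put at "of not less than 51"%, with "a noninferiority threshold Δ=–10"%, "a sample ratio of the study and control groups of 1:1" and "a unilateral test level (α = 0.025"). Power is 80%, loss is 5%, and the result is 202 patients, 101 per arm.
- **Section 2.8 (outcomes).** "Primary outcome: Neurological functional status at 90 days postoperatively". The measure follows: "Patient neurological functional status will be assessed by mRS and NIHSS scores". Neither scale is dichotomised and neither is ranked above the other.
- **Abstract (study outcomes).** It repeats the 90 days and both scales.
- **Section 2.7 (follow-up).** "Patients will undergo follow-up evaluation on days 1, 7, 30, and 90 after surgery", with NIHSS and mRS scored at those visits. The last planned vascular imaging is also on day 90.

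The figure of 180 days appears only in section 2.11.

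**The concern.** A noninferiority trial depends on three things that must refer to the same quantity: the primary endpoint, the margin, and the control rate behind the sample size. Here the rate and margin refer to a proportion at 180 days, while the primary outcome is two scores at 90 days. A margin in percentage points has no meaning for a difference in mRS or NIHSS scores until a score is turned into a yes/no outcome, and section 2.8 does not do that.

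If this stays as written, a reader of the results cannot tell which comparison the -10 points applies to, and the 80% power claim belongs to an endpoint other than the one reported as primary.

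**Working it through.** **Step 1. Reproduce the stated sample size.** Inputs, all from section 2.11: rate 0.51 in both arms, margin 0.10, one-sided alpha 0.025 (z = 1.960), power 80% (z = 0.842), 1:1 allocation, 5% loss.

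n per arm = (1.960 + 0.842)² × (0.51×0.49 + 0.51×0.49) / 0.10² = 7.849 × 0.4998 / 0.01 = 392.3, so 393.

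With 5% loss: 393 / 0.95 = 413.7, so 414 per arm and 828 in total. The plan states 101 per arm and 202 in total, so its figure is not reproduced. A null-restricted variance (about 390 per arm before loss) or a continuity correction (about 413) does not change this.

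Power is Φ(0.10 / SE − 1.960), with SE = √(0.4998 / n):

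- n = 101 per arm: SE = 0.0703, power about 30%.
- n = 96 per arm (about 5% lost): SE = 0.0722, power about 28%.

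One route does come close to 202. It assumes a true rate of 61% in the study arm against 51% in control: 7.849 × (0.61×0.39 + 0.51×0.49) / 0.20² = 95.7, so 96 per arm, then 101 (×1.05) or 102 (÷0.95). Section 2.11 does not state such a benefit.

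**Step 2. Set the powered endpoint beside the primary outcome.**

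| | Section 2.11 | Section 2.8 and abstract | Section 2.7 |
|---|---|---|---|
| Time | 180 days | 90 days | Days 1, 7, 30, 90 |
| Form | One proportion | mRS and NIHSS scores | mRS and NIHSS scores |
| Cut-off for good function | None given | None given | None given |
| Margin | -10 percentage points | None given | Not applicable |

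The entries differ in time point and in form. As scheduled, no assessment falls at 180 days.

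**Step 3. Read 180 d as a slip for 90 d.** The time point then agrees with sections 2.7 and 2.8. The form still does not: the 51% and the margin remain attached to a good-function rate that section 2.8 does not define on either scale.

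**Step 4. What relabelling does to the sample size.** Time does not enter the formula, so changing the label alone leaves 393 per arm (414 with loss). What matters is whether 51% is the right rate for the 90-day endpoint that is chosen. The document gives no other rate. For assumed common rates of 60%, 70%, 80% and 90%, shown only as a range, the number per arm with loss is 397, 348, 266 and 150. All exceed 101.

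**The case against.** The strongest reply is that 180 d occurs once, in a parenthesis, and is probably a slip; mRS and NIHSS are both collected on day 90, so the intended data will exist. It can be added that section 2.12 provides rates and a chi-squared test for count data, so a dichotomised score fits the stated methods, and that a cut-off may sit in a full protocol or SAP that is not shown.

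Part of this stands. A slip is plausible, and a missing cut-off alone could be left to another document. But the article states two endpoints that do not agree, and a SAP cannot decide which of two protocol statements governs. The slip reading repairs the time point and not the form.

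Three stronger readings are tempting and are not supported:

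- *The powered endpoint will have no data at all.* This fails if 180 d is a slip. Nor does the article say that the trial ends at day 90; it only plans nothing later.
- *Two primary scales inflate the type I error.* That assumes that success on either scale is enough. Section 2.8 names one outcome assessed by two scales and gives no such rule. If both had to succeed, the error would not be inflated.
- *NIHSS will be compared in survivors only, which could flatter the arm with more deaths.* No section restricts the analysis to survivors, section 2.12 refers to an intention-to-treat type of analysis, and the handling of deaths is ordinary SAP content.

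**Conclusion.** The point holds as an inconsistency in the current text. Sections 2.7, 2.8 and 2.11 do not describe the same endpoint, and nothing in the article resolves the difference. It should be corrected before the analysis, because the margin, the 51% and the 202 patients all rest on it. The conclusion needs no assumption about mortality, about correlation between the scales, or about how the two scales would be combined.

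The mismatch itself has no single numerical size. Its consequence is that the claimed 80% power does not belong to the stated primary outcome. The failure of 202 to follow from its own inputs (828 does, with equal true rates) is a separate matter that does not depend on the endpoint mismatch. It does mean that correcting the time label alone would leave an unsupported sample size in place.

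**What to change.** Reconcile sections 2.7, 2.8 and 2.11, and the abstract with them:

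1. Name one binary primary endpoint at day 90 to which the -10-point margin applies. One option is mRS 0-2 at day 90, with death (mRS 6) counted as not good. The documents do not dictate this cut-off; the need is for one that is stated.
2. Change 180 d to 90 d in section 2.11.
3. Confirm that 51% is a 90-day rate on that definition, or replace it.
4. Restate the sample size justification for that endpoint, including any assumed true difference, or state the power that 202 patients deliver.
5. Report 90-day NIHSS as a secondary outcome.

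Cost: an amendment to the wording and a repeated calculation. Day-90 mRS is already scheduled, so no visits or data are added. The real downsides are that NIHSS loses primary status and that the restated power may be less favourable than 80%, which could reopen the question of sample size.

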### 2.2. Study population and preoperative evaluation

The study population will include patients with acute ischemic stroke caused by atherosclerotic carotid occlusion and confirmed by imaging (computed tomography angiography (CTA)/magnetic resonance angiography (MRA)/digital subtraction angiography (DSA)) attending Tianjin Huanhu Hospital, and 202 patients are planned to be enrolled: 101 patients in the study group and 101 patients in the control group.

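### With 51% good function in both groups, 202 patients give about 28–31% power for the 10-point noninferiority margin, not the stated 80%

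*Protocol article*

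**What the plan says.** Section 2.11 (Sample size estimation) of the protocol article prints all the inputs and the result together:

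- Outcome rate: "Assuming a rate of good neurological function in both the study and control groups (180 d) of not less than 51" per cent. The same figure applies to both groups and is worded as a minimum.
- Margin: "a noninferiority threshold Δ=–10" per cent.
- Allocation: "a sample ratio of the study and control groups of 1:1".
- Alpha: 0.025, one-sided.
- Power: "a total certainty of 80" per cent.
- Loss: 5%.
- Result: "the total sample size required is 202 patients and 101 patients in each group".

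Section 2.2 repeats the total ("202 patients are planned to be enrolled"), and the Abstract gives the same 101 per group. The article states no expected advantage for the ECASES group.

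**The concern.** When both groups are assumed to have the same rate near 50%, a 10-point margin with 80% power usually needs several hundred patients per group. A requirement of 101 per group therefore looks far too small for the inputs printed beside it.

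The stated power is what readers, the ethics committee and the monitoring committee rely on when they judge whether the trial can answer its question. If power is nearer 30% than 80%, then about seven in ten such trials would fail to show noninferiority even if ECASES performs exactly as well as operator judgement. Such a failure could be misread as evidence against ECASES when it would mainly reflect the trial's size.

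**Working it through.** **Inputs, all from section 2.11.** Rate 0.51 in each group, so a true difference of 0; margin 0.10; one-sided alpha 0.025 (z = 1.960); power 80% (z = 0.842); 1:1 allocation; 5% loss; 101 enrolled per group. Evaluable per group: 101 × 0.95 = 95.95, about 96.

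**Attempt to reproduce 202.** Standard noninferiority formula for two proportions with unpooled variance:

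n per group = (1.960 + 0.842)² × (2 × 0.51 × 0.49) / 0.10² = 392.3, rounded up to 393.

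After 5% loss: 393 / 0.95 = 413.7, so 414 per group and 828 in total. The stated 202 is about a quarter of this (202 / 828 = 0.24) and is not reproduced.

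**Other conventions, keeping 51% in both groups and the 10-point margin.**

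- One-sided alpha 0.05: 310 evaluable, 327 per group after loss.
- One-sided alpha 0.10: 226 evaluable, 238 per group after loss.
- Continuity correction: increases the number, to about 413 evaluable per group.
- Multiplying by 1.05 instead of dividing by 0.95: 413 per group.
- Reading 202 as the number per group: 50–52% power.

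None gives 101 per group.

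**Power of the stated size.** Standard error at 96 per group = √(2 × 0.51 × 0.49 / 96) = 0.0721.

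Power = Φ(0.10 / 0.0721 − 1.960) = Φ(−0.574) = 0.283.

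| Evaluable per group | Normal approximation | Exact binomial enumeration |
|---|---|---|
| 95 | 28.1% | 30.6% |
| 96 | 28.3% | 30.7% |
| 101 (no loss) | 29.5% | 31.1% |

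The exact figures are the same, to the precision shown, for the Wald and Farrington–Manning tests.

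**Precision.** Expected 95% confidence interval half-width = 1.960 × 0.0721 = 0.141, or 14.1 points. With rates near 51%, noninferiority would need an observed advantage for ECASES of about 14.1 − 10 = 4.1 points.

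**Reading 51% as a floor.** Power at 96 per group with equal rates in both groups, normal approximation:

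| Common rate | Power |
|---|---|
| 51% | 28% |
| 60% | 29% |
| 70% | 33% |
| 80% | 41% |
| 90% | 64% |
| 93.5% | 80% |

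**Assumptions that would give about 101 per group.** With a true advantage of 10 points (61% ECASES, 51% control), the distance to the margin becomes 20 points:

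7.849 × (0.61 × 0.39 + 0.51 × 0.49) / 0.20² = 95.7, and 95.7 / 0.95 = 100.8, which rounds up to 101.

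This is not the only fit:

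- 71% v 62%: 7.849 × (0.2059 + 0.2356) / 0.19² = 96.0.
- 86% v 81%: 7.849 × (0.1204 + 0.1539) / 0.15² = 95.7.
- Equal rates of 93.5%: 7.849 × 0.12155 / 0.10² = 95.4.

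A 20-point margin at 51% in both groups comes close but does not match: 98.1, so 99 evaluable and 104–105 per group.

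**The case against.** The strongest defence is that the article gives a minimum rate, not a point value. A design with 61% under ECASES and 51% under operator judgement respects that minimum in both groups and yields 101 per group. An article also condenses a fuller protocol, so an expected advantage may have been dropped in shortening.

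Part of this stands. A reader might infer that the sponsor assumed a 10-point benefit and that this contradicts the text. The article supports neither step. The 61% v 51% pair is a back-calculation; other pairs at or above the floor fit equally well, and a rate stated as a minimum does not exclude unequal rates. The fair statement is that some assumption needed to reach 202 is not stated.

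It is also fair that a single figure of 28% is too definite. It is a normal approximation under exact equality at 51%; exact calculation gives about 31%, and power rises if ECASES is truly better (normal approximation at 96 per group: 44% at +3 points, 55% at +5).

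The defence does not remove the problem. The inputs and the result are printed in one sentence and do not agree. With equal rates the floor helps only near 93.5%, which is implausible beside a planning minimum of 51%. If an assumption was lost in condensing, the published sentence still needs it.

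**Conclusion.** The power claim in section 2.11 is wrong for the assumptions printed with it. With 51% in both groups, the inputs require about 828 patients, and 202 patients give about 28–31% power. The expected interval half-width of about 14 points exceeds the 10-point margin.

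This rests on a two-group comparison of proportions, one-sided alpha 0.025, about 96 evaluable per group after 5% loss, and no true difference between groups. It does not depend on how 202 was obtained. Nor does it show that the trial will fail, since that depends on the true difference, which is unknown.

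**What to change.** Restate section 2.11 so that inputs, sample size and power agree.

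- **Default:** keep 51% in both groups, replace the 80% with about 28–31% power for 202 patients, and add the expected 95% confidence interval half-width of about 14 points.
- **Only if the sponsor confirms that 202 was based on an expected advantage for ECASES:** state the rate assumed in each group, justify it, and also report the 28–31% power under equal rates.

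Either restatement changes wording only and adds no patients. The cost is a less favourable stated power. If the sponsor wants 80% power under equal rates of 51%, about 828 patients would be needed; that would be a redesign, not a correction of the text.
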